### Data Collection and Management:

All pregnant women of gestational age <20 weeks in the participating units will be advised complete blood count. Those having haemoglobin >11g/dl, will have their serum ferritin levels checked. Pregnant women having serum ferritin <30μg/l will be counselled for enrolment into the study and informed consent will be taken after explaining the details of the study. They will be divided into two groups randomly. Therapeutic dose of IV iron will be advised to intervention group and prophylactic dose of oral iron (30-45 mg) will be given to the control group of pregnant women to be continued till delivery. All pregnant women will be followed up till delivery with the usual protocol of monthly visits till 28 weeks then fortnightly visits till 36 weeks and then weekly. Haemoglobin and serum ferritin in both arms will be measured at 28 weeks and 36 weeks of gestation. Development of preeclampsia, preterm birth, blood transfusion, fatigue score, birth weight along with cord blood haemoglobin and serum ferritin will be recorded. Data will be entered into an electronic database (computer software program ASP. NET MVC architecture data collection platform based on SQL 2014 for data normalization) has been purpose designed for the trial with defined multi level user access and separate case report forms for each study visit. The software platform ensures transparent randomisation, allows real-time data acquisition and smooth tracking of the enrolled participants to facilitate standardised, and synchronous data collection across all the study sites, enabling data quality checks and ensuring authenticity of data.

### Data Analysis:

All the statistical analysis will be done on statistical package for social sciences (SPSS). Mean and standard deviation will be calculated for continuous variables like age, gestational age, haemoglobin, serum ferritin levels etc. Frequency and percentages will be calculated for categorical variables like gender. If data are not normally distributed then median will be used. Confounders like age, duration of disease and co morbidities will be controlled through multivariable analysis documented through a statistical analysis plan prepared before the outcome data per group are unblinded. Comparison of outcome will be tested by chi-square and student’s t-test. P value of <0.05 will be significant.

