### Sample Size:

Using haemoglobin at 36 weeks as a continuous outcome measure and to confirm or refute a small to medium effect of screening/intervention vs usual care (0.3 SD difference), based on ? = 0.05 and β = 0.1 (90% power), 235 patients in each group (i.e. 470 patients in total) will be required. Considering a 20% loss to follow-up, the sample size is inflated to 300 patients in each group (i.e. 600 patients in total).

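### The plan names both an unadjusted t-test and a multivariable analysis without saying which is primary, and its example covariates leave out baseline haemoglobin and hospital

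*Protocol article*

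**What the plan says.** The Sample Size section fixes the outcome and the design figures: "Using haemoglobin at 36 weeks as a continuous outcome measure", a "0.3 SD difference", and "235 patients in each group (i.e. 470 patients in total) will be required", which is raised to 300 per arm for 20% loss to follow-up.

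The Data Analysis section then gives two routes to a result. One is a simple comparison: "Comparison of outcome will be tested by chi-square and student’s t-test". The other is adjusted: "Confounders like age, duration of disease and co morbidities will be controlled through multivariable analysis". The detail of the adjusted analysis is left to a statistical analysis plan, to be written before outcome data per group are unblinded. Neither route is called primary.

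On available data, the Recruitment and Data Collection and Management sections have haemoglobin measured at booking, before randomisation. The latter adds: "Haemoglobin and serum ferritin in both arms will be measured at 28 weeks and 36 weeks of gestation". The Trial Design and Study Setting sections name three hospitals.

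**The concern.** Both analyses can be applied to 36-week haemoglobin, and they can fall on opposite sides of P<0.05. A reader of the article cannot tell which one would carry the conclusion.

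The example covariates are also poorly chosen. Adjustment in a randomised trial is done mainly to gain precision from prognostic variables; controlling confounders is the language of observational studies. Booking haemoglobin is probably the most prognostic variable available for later haemoglobin, and hospital is a natural second, yet neither is mentioned. Duration of disease is hard to define in women who have no anaemia and whose low ferritin is first found by the trial's own screening.

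At stake are some precision on the primary outcome and the clarity of the primary analysis. The validity of the randomised comparison is not at stake.

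**Working it through.** **Inputs from the Sample Size section:** difference 0.3 SD, alpha 0.05, power 90%, 235 evaluable per arm, 20% loss, 300 recruited per arm. Sidedness is not stated.

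**Assumed inputs, not in the documents:** correlation r between booking and 36-week haemoglobin, 0.2 to 0.5; share of outcome variance lying between hospitals, 0.01 to 0.10.

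**Step 1: reproduce the plan's figure.** The normal formula for two means, two-sided, is n = 2(1.960 + 1.282)² / 0.3², about 233.5, so 234 per arm. The t-based solution is 234.5, so 235 per arm, as stated. A one-sided test would need only 191, so the plan is two-sided.

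**Step 2: loss to follow-up.** 235 / 0.8 = 293.75, so 294 per arm; the plan rounds up to 300. With 20% lost, 300 × 0.8 = 240 remain per arm. The unadjusted t-test then has 90.7% power (t-based; 90.8% by the normal formula). The design target is met.

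**Step 3: adjust for baseline haemoglobin.** ANCOVA reduces the residual SD by the factor √(1 − r²), so the effective standardised difference is 0.3 / √(1 − r²). The number per arm giving the same precision as 235 unadjusted is 235(1 − r²).

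| r (assumed) | effective difference | power at 240 per arm (t-based) | equivalent n to 235 |
|---|---|---|---|
| 0 (t-test) | 0.300 | 90.7% | 235 |
| 0.2 | 0.306 | 91.7% | 226 |
| 0.3 | 0.314 | 93.0% | 214 |
| 0.4 | 0.327 | 94.7% | 197 |
| 0.5 | 0.346 | 96.6% | 176 |

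The Abstract and Table-I restrict entry to haemoglobin from 11 to 13. Restricting the range of a baseline variable lowers its correlation with the outcome, so the upper rows of the table are the more plausible.

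**Step 4: adjust for hospital alone.** With residual SD factor √(1 − share), power at 235 per arm (normal formula) goes from 90.2% to between 90.5% and 92.9% for shares of 0.01 to 0.10. The Allocation section does not state stratification by hospital, so the case for including it is its prognostic value.

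**Step 5: the 28-week haemoglobin.** It is measured after randomisation and the intervention acts on it. As a covariate it would remove part of the effect being estimated. It can enter only as a repeated outcome alongside the 36-week value.

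**The case against.** The strongest reply is that this is a journal article and that it defers the adjusted analysis to a statistical analysis plan that is not shown. The final covariates and the primary model may be settled there, before outcome data per group are unblinded. Much of this stands. The word 'like' leaves the covariate list open, so baseline haemoglobin and hospital are unnamed and not excluded. What the reply does not cover is what the article itself chose to print: two analyses side by side with no order between them, and an example covariate that does not suit the population.

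A reader might infer several stronger things that the documents do not support:

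- **That the trial discards its baseline data or is underpowered.** A multivariable analysis is planned, and the t-test is valid for a 1:1 randomised comparison and meets the stated power.
- **That duration of disease is recorded nowhere.** The case report forms are not shown, so this cannot be checked.
- **That the comparison is biased because women who deliver before 36 weeks drop out of it.** The article states no complete-case rule. If early-delivery rates differed by 4 to 6 percentage points between arms and those women differed by 0.3 to 0.5 SD (all assumed), the shift would run from 0.04 × 0.3 = 0.012 to 0.06 × 0.5 = 0.03 SD, which is 4% to 10% of the 0.3 SD target. ANCOVA on 36-week values would leave out the same women as the t-test, so this argument does not favour one over the other.

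**Conclusion.** The concern holds as a point about naming the primary analysis and about efficiency. The article gives two analyses without saying which decides the trial, and its example covariates include one with no clear meaning here while omitting two useful ones already to hand. The sample size reproduces and the t-test is sound.

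The gain at 240 per arm is 1.0 power point at r = 0.2, 2.3 at r = 0.3 and 5.9 at r = 0.5. It rests on the 0.3 SD difference, 20% loss and an assumed correlation that is more likely low than high. The improvement is modest but costs nothing. If the unseen analysis plan already names a baseline-adjusted primary model, only the article's wording needs correction.

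**What to change.** Name one primary analysis: a linear model (ANCOVA) of 36-week haemoglobin on arm, booking haemoglobin and hospital, reporting the adjusted mean difference with its 95% CI. Keep Student's t-test as a sensitivity analysis. Drop duration of disease from the examples, and describe the covariates as prognostic variables and not as confounders.

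If the 28-week haemoglobin is to be used, let it enter only as a repeated outcome in a linear mixed model, with the arm difference taken at 36 weeks. That model uses women who have a 28-week value but none at 36 weeks, under a missing-at-random assumption that should be stated. For women who deliver before 36 weeks it implicitly predicts a value that never existed, and the plan should say so.

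The cost is wording only. Booking haemoglobin and hospital are already known for every woman, the planned software fits both models, and the sample size stays as it is.

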### Data Monitoring:

Trial steering committee with an independent chair and membership including a patient representative will oversee the study. Data monitoring committee will perform confidential interim analyses, which may be used to determine if an effect is observed and if the study should continue to its planned sample size. Any adverse reaction to IV Iron or blood transfusion will be noted and entered in specific transfusion reaction registers in wards according to hospital protocol. Independent data monitoring committee will systematically review all trial related activities, data entry, will assess compliance with regulatory requirements for clinical trial protocol and clinical quality management plan by principal investigator and all sites support personnels and audit trial quarterly to identify potential risks and help to ensure that compliance issues do not jeopardize the trial.

### Patient and public involvement:

A lay patient representative (patient with lived experience) has been included in the trial steering committee. The representative has given advice on the protocol and consent procedures submitted for ethics committee approval and will give oversight to the study during its conduct.

### Ethics and Dissemination:

The study will tell us whether by screening serum ferritin early in nonanemic pregnant women and replenishing their iron stores will reduce the incidence of anemia in pregnant women, improve birthweight and preventing complications.

### Ethics Approval:

Ethics approval has been granted by institutional review board of Services Institute of Medical Science, Lahore: IRB/2019/599/SIMS (dated 05 December 2019), Allama Iqbal Medical College, Lahore: 54^th^/ERB (dated 17 December 2019) and Fatima Jinnah Medical University, Lahore; 34-Res-Proposal-Gynae-1/ERC (dated 29 October 2020). Appendix No.1.

### Consent:

Informed consent will be taken by the investigators conducting the trial in outpatient departments on specially designed consent proformas. Appendix No.2

### Access to Data:

Data monitoring team, Trial Technology team will be given access to the data.

### Dissemination Policy:

Trial findings will be published in peer reviewed journals and propagated in different conference meetings, providing much needed evidence to inform clinical and public health actions in this area. Dissemination will also be done through amendments in ward protocols.

Protocol prepared according to Spirit checklist (https://www.spirit-statement.org/)^28^
